### Statistical methods and analysis

#### Utilization rates

Utilization rates will be estimated for each provider for every BE module component to which they apply (see Table 1); these rates will be summarized across physicians with 95% confidence intervals. To assess clinical value, each patient will be classified as CW compliant or not using the definition above; this indicator will be averaged across patients within a provider to calculate a provider-level compliance rate. These will also be summarized with 95% confidence intervals. The pilot study will provide critical estimates of utilization rates and clinical outcomes, allowing for refinement of the clinical trial design (Additional file 1). Specifically, following completion of the pilot study, the pruning decisions described below can be made to eliminate less effective approaches and guide future module development decisions.

#### Pilot phase qualitative user feedback

As outlined in Table 2, user feedback collected in the pilot phase will be analyzed with both pragmatic and academic goals. In order to maintain the timeline necessary for iterative product development, all user feedback will be summarized from researcher notes, providing near real-time feedback for module development and iteration. Simultaneously, systematically collected user feedback will be analyzed for more detailed usability findings deemed valuable by the research team for module implementation and academic dissemination using Dedoose, a software package that can integrate transcripts, pictures, memos, and other materials. Procedures recommended by Patton and others that focus on developing coding protocols to highlight issues, problems, and potential recommendations will be used [58]. The goal of these analyses is to identify key barriers and facilitators, as well as any emerging themes related to the use of the BE-EHR module to influence provider adherence to the CW guidelines.

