#### User testing (aim 1, phase 2)

Prior studies also established a clear link between the user-centered design process and successful implementation of clinical decision support tools within the EHR [49–51]. Upon completion of the design-thinking workshop and subsequent development of nudge prototypes, nudges will be further refined through a tailored, multi-phase feedback gathering and user testing process [46]. This pre-clinical testing serves as a clinical laboratory for building successful workflow-integrated tools with a high likelihood of adoption and adherence [41, 44, 52]. In addition to key informant interviews and group interviews with users as described above, a variety of methods for collecting both qualitative as well as quantitative user feedback will be selected. See Table 2 for user research methodologies to be employed on an as needed basis according to fit based on type of module, content, frequency of clinician “exposure,” and response to the module.

**Table 2 Tab2:** Possible research methods for user testing

User testing methods	Description	Predicted frequency and time point
Key informant interviews	Semi-structured interviews with individual or small group (2–3) experts in primary care, geriatrics, EHR, diabetes, and other relevant fields	6–8 informants, 1–2 interviews each
Group interviews	Semi-structured interviews with groups of 4–6 clinicians	Pre- and post vanguard
“Ride along” observation	Individual observation session of clinician interaction with EHR real time, in situ	6–8 sessions per vanguard and pilot
Think-aloud usability testing [53]	Individual observations in “lab” of clinicians verbalizing all thoughts as they interact with the module following a carefully scripted series of EHR tasks	4–6 observations as needed in pilot
Near live [50, 53, 55]	Individual observations in “lab” of clinicians interacting with simulated data and patient actors to realistically model clinical use of module	4–6 observations as needed in pilot
Live [51, 56]	Individual observations of clinicians in situ using the tool in actual patient care	3 observations as needed in pilot

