Clinical decisions in accordance with the CW guideline will be drafted and approved by clinical experts on the research team and will guide actions prompted by text and visuals in the CDS modules. Example clinical actions include switching a patient’s medication to metformin, reducing the dose, or removing the prescription of an alternative medication for patients with an HbA1c laboratory value too tightly controlled given their calculated life expectancy. Once the new module has stabilized within the vanguard sites (workflow issues are resolved and clinician usage is stable) (aim 1), the tool will be activated at the pilot sites (aim 2).

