### Aim 2: Pilot testing the BE-EHR modules (phase 3)

To assess the utilization and feasibility of the new tools and generate preliminary estimates of clinician compliance with the CW guideline, a 6-month, single-arm pilot study of the BE-EHR module will be conducted in six outpatient primary care clinics.

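### Pilot-phase feedback is meant to feed module iteration, but the 30% retention rule uses a utilization rate with no split by component version

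*Protocol article*

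**What the plan says.** Before the pilot, the section on algorithms for CDS activation sets a condition: "Once the new module has stabilized within the vanguard sites (workflow issues are resolved and clinician usage is stable) (aim 1), the tool will be" switched on at the pilot sites.

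During the six-month pilot, the section Pilot phase qualitative user feedback states that "user feedback collected in the pilot phase will be analyzed with both pragmatic and academic goals". The practical purpose is given next: "In order to maintain the timeline necessary for iterative product development". The means to that end follows in the same sentence of the article: "all user feedback will be summarized from researcher notes, providing near real-time feedback for module development and iteration".

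For the analysis, Utilization rates plans one rate for each provider and each applicable component, summarized across physicians with 95% confidence intervals. It mentions neither version nor calendar period. The timing of the decision is stated there too: "following completion of the pilot study, the pruning decisions described below can be made to eliminate less effective approaches". Intervention pruning supplies the criterion. A tool used in more than 30% of its opportunities is kept, within a set of mixed-methods criteria. Tools that cannot be measured this way, such as reworded HbA1c lab reports, are assessed from qualitative feedback.

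The nearest text to a safeguard is under Limitations, where longitudinal data are planned on the order and timing of clinicians' exposure to the different nudges. Successive versions of one nudge are not mentioned.

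**The concern.** The pilot has to say which tools go into the finalized module and, according to Limitations, which nudges a later randomized trial would use. That calls for a utilization rate belonging to an identifiable tool. If the feedback loop leads to a changed trigger, default or wording while the pilot is running, a rate taken over all opportunities averages the superseded tool and its replacement. It then describes neither.

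A tool that was repaired could miss the threshold because of its earlier form. A tool that a later change made worse could pass because of its earlier form. The provider-level compliance rate would also be measured under a changing intervention, though no threshold is attached to it.

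**Working it through.** There is no plan figure to reproduce. The article gives no sample size or power, and 30% is a chosen cut-off. The check is whether mixing versions can change the decision at plausible rates.

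**Inputs from the article (Intervention pruning):** the retention threshold of more than 30%, and the cited utilization range of 5–40% for common CDS tools.

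**Assumed inputs:** the early-version rate p_E and final-version rate p_F, both kept within 5–40%, and f, the share of opportunities falling under the early version. For simplicity f is taken as equal across providers, so that the same formula holds for the average of the provider rates.

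**Formulas:**
- Pooled rate = f × p_E + (1 − f) × p_F
- Share at which the pooled rate equals 30%: f* = (p_F − 0.30) / (p_F − p_E)

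**Results:**

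| p_E | p_F | Final version alone | f = 1/6 | f = 1/3 | f = 1/2 | f* |
|---|---|---|---|---|---|---|
| 20% | 35% | passes | 32.5%, passes | 30.0%, does not pass | 27.5%, does not pass | 0.05/0.15 = 1/3 |
| 40% | 25% | does not pass | 27.5%, does not pass | 30.0%, does not pass | 32.5%, passes | 0.05/0.15 = 1/3 |
| 5% | 40% | passes | 34.2%, passes | 28.3%, does not pass | 22.5%, does not pass | 0.10/0.35 = 0.286 |

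For example, in the first row at f = 1/2: 0.5 × 20% + 0.5 × 35% = 27.5%.

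The rule requires more than 30%, so exactly 30.0% does not meet it. In the first row the pooled rate therefore fails once f is one third or more, although the final version passes. In the second row it passes once f exceeds one third, although the final version fails. If opportunities accrue evenly, f = 1/3 is a change made two months into the six. A change after one month (f = 1/6) gives the same decision as the final version alone in all three rows, so early revisions do less harm.

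**The case against.** The strongest objection is that no sentence in the article puts a revised build into use at the pilot sites. The quoted text fixes how quickly feedback is summarized, not when changes are deployed. Utilization rates speaks of guiding future development once the pilot is complete, and later sections refer to an eventual and a finalized module. All of this fits a reading in which changes wait. The objection stands to this extent: the mixture of versions is conditional. It does not remove the point, because near real-time summaries justified by an iteration timeline suggest that changes are at least possible, and nothing rules them out.

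A reader might infer that the article contradicts itself by stabilizing the module and then iterating it. It does not. Stabilized is defined as workflow issues resolved and usage stable, which is not the same as frozen. It also makes large redesigns less likely. The two passages are in tension, no more.

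Table 2 might be read as further evidence, since it lists think-aloud and near-live testing as "4–6 observations as needed in pilot". These are optional laboratory sessions, and holding them changes nothing in the live module.

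It is also fair to say that the 30% criterion is a retention rule, and that the article does not say a tool at or below 30% is dropped automatically. The effect on an individual tool may be softened by the qualitative evidence.

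Finally, version logging could be left to a full protocol or SAP. But the article itself fixes the unit of the rate, the threshold and the timing of the decision, and itself introduces pilot-phase iteration. Which version the rule refers to is part of that rule.

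**Conclusion.** The point holds in conditional form. The article provides for iteration from pilot feedback and applies a 30% rule to a rate without a version, and does not say how the two fit together. If a component is revised during the pilot, the rule can give the wrong answer in either direction. In the two 15-point examples this happens once about one third of opportunities fall under the earlier version.

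These sizes rest wholly on assumed rates and an assumed split. They show that a reversal is possible within the cited range; they do not predict one. A component that is not revised, or is revised only in the first weeks, is little affected. Tools outside the 30% rule are not affected by this argument.

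A reader might conclude that the module must be frozen for the pilot, or that only a fixed final window of weeks should count. The documents do not support requiring either. Iteration is a declared part of the approach, and the problem is solved once the rule refers to an identifiable version.

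**What to change.** In Utilization rates, Pilot phase qualitative user feedback and Intervention pruning:

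1. Record the build version and change dates of each component in the EHR reports already planned.
2. Estimate utilization by version.
3. Apply the 30% rule to opportunities under the version to be carried forward, and report the rate pooled over all versions as secondary.
4. Report compliance with the dates of module changes shown.

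If no change to content or triggers is intended during the pilot, a sentence to that effect in Pilot phase qualitative user feedback replaces all four steps.

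The cost is a version field and a few lines of text. The statistical cost falls only on revised components, which have fewer opportunities and wider intervals. If one third of opportunities fall under an earlier version, two thirds remain. At the same rate, and with every provider still contributing, the interval is then at most √(1/(2/3)) = √1.5 ≈ 1.22 times as wide, and less where differences between providers dominate.

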#### Intervention pruning

We will apply mixed methods “pruning criteria” to eliminate less effective approaches. To address the evaluation of individual components, utilization measures will be assessed to determine the value of the tool for incorporation into the eventual BE-EHR module. If the CDS tool is utilized in more than 30% of opportunities (e.g., if a suggested default is accepted in more than 30% of cases), then this tool will be retained in the module. While there is no gold standard threshold for what a “useful” CDS tool utilization rate should be, studies have noted common CDS tools with utilization rates between 5 and 40% depending on the type of CDS and the risk of ignoring it [59–61]. Furthermore, while low utilization rates may prove clinically worthwhile in high-risk patient safety situations, lower risk scenarios like the CW diabetes guidelines for older adults dictate the need for a stronger mean adoption rate [49]. Certain tools will not be evaluable with this criterion, for example, the effect of adjusting the language on HbA1c lab reports. For these tools, qualitative user feedback during usability testing and brief interviews with key informants during piloting will be used to complement the utilization pruning criterion.

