##### Identification of behavioral economic approaches and module opportunities and utilization measures

Initially, the BE and CDS literature will be further reviewed and candidate approaches selected for evaluation by the research team. Based on prior work and the current literature, Table 1 outlines example BE concepts and relevant CDS tools to support the implementation of each BE approach, along with utilization measures available to assess process outcomes.

**Table 1 Tab1:** Behavioral economic strategies and associated module opportunity examples

BE strategy	Module opportunity	Utilization measure
Suggest alternatives [48]	Alert suggests metformin when trying to prescribe other diabetes medication in CW eligible patient	Percentage of eligible alerts where alternative is selected
Accountable justification [48]	Subcomponent of alert asking for justification if prescribing diabetes medication other than metformin	Percentage of eligible alerts where justification is provided (vs. only “clicked through”)
Defaults [30, 49]	Default all diabetes management order sets to suggest metformin in eligible patients	Percentage of order sets where clinician changes the default option
Anchoring [50]	Update HbA1c lab reports for CW eligible patients to show less aggressive treatment goals	Qualitative feedback and percentage of CW compliant patients pre- and post implementation update
Peer comparisons/norming [48, 51]	Modify clinician quality and safety dashboard to visualize diabetes management peer comparisons with color codes to indicate relative performance	Number of views of the peer comparison dashboard
Availability bias [30]	Medication preference list prioritizes metformin	Number of prescriptions for metformin initiated from preference list

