### Limitations

As with any study design, there exist some limitations. First, the sample size that would be required to adequately power the present study is beyond the scope of this work. Hence, results from this pilot study will influence the decision of whether to push forward with a fully developed randomized controlled trial using only those nudges that show promise. Furthermore, with the incorporation of nudges (see Table 1) simultaneously across the EHR, it will be challenging to determine exactly which BE strategy or intervention has the strongest impact. Care will be taken to perform statistical analyses using adjustments and gathering summary statistics for different groups of nudges that are less likely to co-occur. Furthermore, we will collect information longitudinally to assess the order and timing with which clinicians were exposed to various nudges. As a pragmatic study, however, we are testing effectiveness in a real-world setting, for which clinicians in practice will be exposed to multiple nudges in combination or simultaneously, making the present design useful for assessing the overall impact in the EHR.

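### For order-set defaults and similar components, the 30% retention rule measures use and not effect, because it takes no account of how often clinicians made the same choice before the nudge

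*Protocol article*

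**What the plan says.** The Intervention pruning section opens with the purpose: "We will apply mixed methods “pruning criteria” to eliminate less effective approaches". The condition for keeping a component is given next: "If the CDS tool is utilized in more than 30% of opportunities (e.g., if a suggested default is accepted in more than 30% of cases"). A component that meets this condition faces no second quantitative hurdle and is kept. The Utilization rates section repeats that pruning after the pilot is meant to weed out the less effective components.

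The cut is supported by the usage of other decision-support tools: "studies have noted common CDS tools with utilization rates between 5 and 40% depending on the type of CDS and the risk of ignoring it". The section adds that a lower-risk setting such as this one calls for higher adoption.

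Some tools are exempt: "Certain tools will not be evaluable with this criterion, for example, the effect of adjusting the language on HbA1c lab reports". For those, qualitative feedback is used.

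The design has no comparator: "a 6-month, single-arm pilot study of the BE-EHR module will be conducted in six outpatient primary care clinics". In Table 1 one measure has a before-after element, in the anchoring row (the laboratory report): "percentage of CW compliant patients pre- and post implementation update". The other rows are measured after activation only.

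Under Limitations, the pilot results feed the decision "whether to push forward with a fully developed randomized controlled trial using only those nudges that show promise".

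**The concern.** The rule has two inputs: how often the component was used after activation, and how often it could have been. When the counted action is one that clinicians also take unprompted, such as ordering metformin from a diabetes order set, acceptance includes everyone who would have ordered it anyway. A default that changes nobody's behaviour then has an acceptance rate equal to the background rate, and it passes whenever that rate lies comfortably above 30%.

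This matters because the text presents the rule as a filter on effectiveness and lets it decide what enters the finished module and, possibly, a randomized trial. A component could go forward as promising on the strength of existing practice alone.

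**Working it through.** **1. Is there a figure to reproduce?** No. The 30% is a chosen cut, and the Limitations section says that adequate power is out of scope. What can be checked is how the rule behaves.

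**2. Which components are affected?** Taking the Table 1 measures in turn:

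- *Defaults:* affected. The action can occur without the nudge, and a default is the rule's own example. Table 1 counts how often the default is changed, whereas the pruning rule counts how often it is accepted. These are complements, so acceptance above 30% means change below 70%.
- *Preference list (metformin prescriptions started from it):* affected only if the count is turned into a rate, since as listed it has no denominator.
- *Suggested-alternative alert:* little affected. It fires once another drug is being ordered, so most clinicians who would have chosen metformin anyway are already excluded.
- *Justification entry and dashboard views:* not affected. Neither exists before the nudge.
- *Laboratory-report anchoring:* exempt from the cut, and the only row with a before-after measure.

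So no component judged by the 30% cut has a planned background rate.

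**3. Chance that a component with no effect is kept.** Let n be the number of opportunities and p the background rate. With no effect, accepted cases X follow Binomial(n, p), and the component is kept if X > 0.30n. For n = 100 that is P(X ≥ 31). The article gives neither n nor p, so both are assumed.

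| Background p | n = 50 | n = 100 | n = 200 | n = 500 |
|---|---|---|---|---|
| 20% | 3% | 1% | 0% | 0% |
| 25% | 16% | 10% | 5% | 0.5% |
| 30% | 43% | 45% | 47% | 48% |
| 35% | 72% | 83% | 92% | 99% |
| 40% | 90% | 98% | 99.8% | 100% |
| 50% | 99.7% | 100% | 100% | 100% |

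The switch point is a background of about 30%. More data make the wrong answer more certain above that point.

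**4. Clustering within providers.** With 20 providers, 10 opportunities each and an intraclass correlation of 0.10 (all assumed; beta-binomial simulation), the chance is 11% at a background of 25%, 47% at 30%, 85% at 35% and 98% at 40%. The pattern is the same.

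**5. Would a significance test be a better rule?** Suppose a component were kept only if the lower 95% limit of the post-minus-pre difference exceeds zero (Wald, equal n per period, independent events). A component with no effect is then kept about 2.5% to 2.8% of the time at backgrounds from 20% to 50%. But the article's only cited effect, in the Background section, is roughly 5–7%, for antibiotic prescribing. For a rise from 30% to 36%, the difference is 0.06 and its standard error is √[(0.30×0.70 + 0.36×0.64)/n]. At n = 100 the standard error is 0.066, and by simulation such a component is kept 15% of the time at n = 100, 25% at n = 200 and 52% at n = 500. In an unpowered pilot that test would often discard useful components.

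**The case against.** The strongest reply is that this is a usage rule in a feasibility pilot. The article speaks throughout of utilization and adoption, its hypothesis is relatively high utilization, and any later randomized trial could test effect. That largely stands, and it is why the cut itself can remain. It does not remove the mismatch, because two sections say that the rule screens for effectiveness. The label of mixed methods does not close the gap either: qualitative feedback is described for tools that the cut cannot evaluate, and no condition is stated that would remove a tool passing 30%. The Limitations section concedes that nudges are hard to separate from one another, but it does not mention background prescribing.

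A reader might infer three stronger claims that the article does not support:

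- *The rule fails for every component.* It does not, as the component list shows.
- *Ineffective components will in fact be kept.* No background rate is given, so nothing shows that any planned component lies above 30%. Table 1 also lists examples only.
- *The rule wrongly drops a nudge that lifts a rare action, say from 5% to 25%.* By arithmetic such a nudge would usually miss the cut (about 90% of the time at n = 100). But the article gives a deliberate reason for wanting stronger adoption in a lower-risk setting, and it states only when a tool is kept; removal of every tool below 30% is an inference.

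**Conclusion.** The point holds in a limited form. For components whose counted action can occur without the nudge (order-set defaults, and the preference list if expressed as a rate), use above 30% cannot show that behaviour changed, so the rule does not deliver the purpose stated for it. If the background rate is well below 30%, the practical harm is small (about 1% at a background of 20%). At 30% it is close to a coin toss, and from 35% upwards a component with no effect is usually kept (83% at 35%, 98% at 40%). These figures rest on an assumed 100 independent opportunities. The clustered check, with different assumptions, changes them little. The choice of 30% as a usage threshold is not in itself an error.

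**What to change.** For the affected components only:

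1. Extract from the EHR the rate of the same action in eligible patients at the same clinics over the 6 months before activation.
2. Report the post-minus-pre difference, with a 95% confidence interval that allows for clustering by provider, beside the 30% utilization rate.
3. In the pruning decision, do not count acceptance at or below the pre-activation rate as evidence that the component works.
4. Keep 30% as a usage or feasibility criterion, and state under Utilization rates and Intervention pruning that it does not by itself measure effectiveness. Do not replace it with a significance test.
5. Express the default measure in the same direction (accepted or changed) in Table 1, Outcomes and Intervention pruning.

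The cost is one small retrospective query for each affected component and a few sentences, with no new patients, sites or procedures. The before-after difference remains open to secular trend and to the joint effect of nudges switched on at the same time, which the Limitations section acknowledges. It therefore informs the decision but does not isolate one component's effect.
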